### Grapefruit juice

It is not recommended to consume grapefruit juice while on olaparib therapy.

### Contraception

Women of childbearing potential and their partners, who are sexually active, must agree to the use of one highly effective forms of contraception and their partners must use a male condom (as described in Appendix C). This should be started from the signing of the informed consent and continue throughout the period of taking study treatment and for at least 6 months after last dose of study drug(s), or they must totally/truly abstain from any form of sexual intercourse (as described in Appendix C).

For details of acceptable methods of contraception refer to Appendix C Acceptable Birth Control Methods.

## Discontinuation of investigational product

Patients may be discontinued from investigational product (IP) in the following situations:

Patient decision. The patient is at any time free to discontinue treatment, without prejudice to further treatment

Adverse Event

Bone marrow findings consistent with myelodysplastic syndrome (MDS)/acute myeloid leukaemia (AML)

Severe non-compliance with the study protocol

Disease progression (unless in the investigator’s opinion the patient is benefiting from the treatment and does not meet any other discontinuation criteria)

### Procedures for discontinuation of a patient from investigational product

At any time, patients are free to discontinue investigational product or withdraw from the study, without prejudice to further treatment. A patient that decides to discontinue IP will always be asked about the reason(s) and the presence of any adverse events. Adverse events will be followed up and all unused study drug should be returned by the patient.

By discontinuing from IP, the patient is not withdrawn from the study unless the patient withdraws consent to participation in the study. Patients should be followed for progression (if discontinuation in the absence of progression), PFS2 and OS following treatment discontinuation as per the protocol schedule.

Any patient discontinuing investigational product should be seen at 30 days post discontinuation for the evaluations outlined in the study schedule. The patient’s tumour status should be assessed clinically and, if appropriate, disease progression should be confirmed by radiological assessment. After discontinuation of study medication, the principal Investigator/Sub-Investigator will perform the best possible observation(s), test(s) and evaluation(s) as well as give appropriate medication and all possible measures for the safety of the patient. In addition, they will record on the eCRF the date of discontinuation, the reasons, manifestation and treatment at the time of discontinuation. If patients discontinue study treatment, the AstraZeneca monitor must be informed immediately. Patients will be required to attend the treatment discontinuation visit. The patient should return all study medication.

After discontinuation of the study medication at any point in the study, all ongoing AEs or SAEs must be followed until resolution unless, in the Investigator’s opinion the condition is unlikely to resolve due to the patients underlying disease, or the patient is lost to follow up. All new AEs and SAEs occurring during the 30 calendar days after the last dose of study medication must be reported (if SAEs, they must be reported to AstraZeneca within 24 hours as described in Section [6.4](#_Reporting_of_serious)) and followed to resolution as above. Patients should be seen at least 30 days after discontinuing study medication to collect and / or complete AE information. For guidance on reporting adverse events after the 30 day follow up period see Section 6.3.1.1.Any patient who has not yet shown disease progression at withdrawal from IP should continue to be followed as detailed in Table 2.

All patients should be followed for survival, up to the final analysis.

If a patient is withdrawn from study, see Section 3.10.

## Criteria for withdrawal

Reasons for withdrawal from the study:

Voluntary withdrawal by the patient who is at any time free to discontinue their participation in the study, without prejudice to further treatment.

Incorrectly enrolled patients i.e., the patient does not meet the required inclusion/exclusion criteria for the study.

Patient lost to follow-up.

Death.

Withdrawal of the informed consent.

### Screen failures

Screening failures are patients who do not fulfil the eligibility criteria for the study, and therefore must not be enrolled. These patients should have the reason for study withdrawal recorded as ‘Did not meet Eligibility Criteria’ (i.e., patient does not meet the required inclusion/exclusion criteria), and screening failure/ study withdrawal should be noted. This reason for study withdrawal is only valid for screen failures (not enrolled patients). Patients who were screen failures may be re-enrolled and re-screened if in the opinion of the Investigator, the reason(s) for earlier withdrawal no longer applies. Patients cannot re-enter the study if dosed and subsequently withdrawn from the study.

### Withdrawal of the informed consent

Patients are free to withdraw informed consent from the study at any, without prejudice to further treatment.

A patient who withdraws consent will always be asked about the reason(s) and the presence of any adverse events (AE). The Investigator will follow up AEs outside of the clinical study.

If a patient withdraws from participation in the study, then his/her unique enrolment number cannot be reused. Withdrawn patients will not be replaced.

If a patient withdraws consent, they will be specifically asked if they are withdrawing consent to:

- Withdrawal of further participation in the study including any further follow up (e.g., survival calls)
- withdrawal of consent to the use of their study generated data
- withdrawal to the use of any samples

## Discontinuation of the study

The study may be stopped if, in the judgment of AstraZeneca, trial patients are placed at undue risk because of clinically significant findings that are not considered to be consistent with continuation of the study.

Regardless of the reason for termination, all data available for the patient at the time of discontinuation of follow-up must be recorded in the CRF. All reasons for discontinuation of treatment must be documented.

In terminating the study, the Sponsor will ensure that adequate consideration is given to the protection of the patients’ interests.

# Study plan and timing of procedures

**4.1 Study schedule**

Table 1 Study Schedule Screening

| **Day** | -28 to –1  **(First visit)** |
| --- | --- |
| Informed consent | X |
| Demographics | X |
| Medical and surgical history | X |
| Prior cancer therapies including radiotherapy, response to current chemotherapy regimen | X |
| History of blood transfusions^a^ | X |
| Inclusion/exclusion criteria | X |
| ECOG Performance Status (0-1) | X |
| Physical examination | X |
| Vital signs, body weight, (includes blood pressure [BP] and pulse) | X |
| ECG^b^ | X |
| Haematology / clinical chemistry^c^ | X |
| Urinalysis | X |
| Pregnancy test^d^ | X |
| Tumour Assessment (CT or MRI according to RECIST 1.1 criteria)^e^ | X |
| Blood sample for disease specific marker (CA-125) | X |
| Blood sample for determination of *gBRCA* and other non *BRCA* germline HRR status^fh^ | X |
| Tumour sample for determination of *sBRCA* and other non-*BRCA* HRR gene mutation status^gh^ | X |
| Adverse Events (from time of consent) | X |
| Relevant concomitant medications | X |

^a^ Include history of blood transfusion within previous 120 days from start of study treatment and the reasons e.g. bleeding or myelosuppression.

^b^ ECG should be performed once the patient has been in the supine position for at least 5 minutes.

^c^ Coagulation test should be performed at screening and if clinically indicated. For a list of all required laboratory tests please refer to Section [5.2.1](#_Laboratory_safety_assessments).

^d^ Women of child-bearing potential must have a negative urine or serum pregnancy test within 28 days prior to starting treatment and a confirmatory test before treatment on Day 1. If results are positive, the patient is ineligible/must be discontinued from the study.

^e^ RECIST assessments will be performed using CT or MRI scans of neck, chest, abdomen, pelvis. Any other areas of disease involvement should be additionally imaged based on the signs and symptoms of individual patients. Baseline assessments should be performed no more than 28 days before the start of study treatment, and ideally should be performed as close as possible to the start of study treatment.

^f^ The remaining samples will be used for exploratory analysis: BRCA and HRR mutation status in the cell-

free DNA

^g^ The remaining samples will be used for exploratory analysis:Immune-markers PD-L1

h The remaining samples will be used for exploratory analysis: HRD status

| Table 2 Study Schedule – On Study Treatment and Discontinuation | | | | | | | | |
| --- | --- | --- | --- | --- | --- | --- | --- | --- |
| Visit Number | 2 | 3 | 4 | 5 | 6 | Visit No. 7 onwards  Subsequent on treatment visits every 4 or 12 weeks^a^  Tumour assessment visits every 12 or 24 weeks^a,f^ | Study treatment discontinued | Follow-up 30 days after last dose of IP |
| Day | 1 | 8 | 15 | 22 | 29 | Day 1of next visit period  (Visit 7 equals day 57 then visit 8 equals day 85 etc) |  |  |
| Visit Window |  | *±3d* | *±3d* | *±3d* | *±3d* | *±3d* | *±7d* | *±7d* |
| Enrolment | X |  |  |  |  |  |  |  |
| Physical exam^c^ | X^b^ |  |  |  |  |  |  |  |
| Vital signs, body weight (includes BP, pulse and temperature) ^c^ | X^b^ |  |  |  |  |  |  |  |
| ECOG performance status | X |  |  |  |  | X | X |  |
| ECG^c^ | X^b^ |  |  |  |  |  |  |  |
| Haematology / clinical chemistry^d,k^ | X^b^ | X | X | X | X | X | X | X |
| Urinalysis^c^ | X^b^ |  |  |  |  |  |  |  |
| Pregnancy test ^e^ | X |  |  |  | X | X |  |  |
| Blood sample for disease specific marker (CA-125) ^k^ | X |  |  |  | X | X | X |  |
| Tumour Assessment (CT or MRI according to modified RECIST 1.1)^f^ |  |  |  |  |  | X^f^  [Every 12 weeks (±7d) ^f^] |  |  |
| Adverse Events ^g,k^ | X | X | X | X | X | X | X | X |
| Concomitant medications including blood transfusions | X | X | X | X | X | X | X | X |
| Olaparib dispensed/ returned ^h,k^ | X |  |  |  | X^h^ | X^h^ | X |  |
| Subsequent cancer therapy following discontinuation of study treatment ^i^ |  |  |  |  |  |  |  | X |
| Time to second progression ^j,k^ |  |  |  |  |  | X |  |  |
| Survival ^k^ |  |  |  |  |  | X |  |  |

^a^ Visit to take place on Day 1 of a 4 week (28 day) visit period up to 120 weeks (if not progressed and still on treatment, or on study treatment post progression), then on day 1 of a 12 week visit period relative to date of enrolment.

^b^ If assessed within 7 days before enrolment and meets the stated eligibility criteria (if applicable), it does not need to be repeated on Day 1 of study treatment unless investigator believes that it is likely to have changed significantly.

^c^ To be additionally performed if clinically indicated at any other time.

^d^ Safety blood samples do not need to be repeated on Day 1 of study treatment if assessed at least 3 weeks after the last dose of chemotherapy but within 7 days before starting study treatment, unless the investigator believes that it is likely to have changed significantly. Coagulation test should be performed at screening and if clinically indicated. For a list of all required laboratory tests please refer to Section [5.2.1](#_Laboratory_safety_assessments).

^e^ Pregnancy tests on blood or urine samples will be performed for women of childbearing potential within 28 days prior to the start of study treatment, on Day 1 of the study prior to commencing treatment, at the time points shown in Table 2 during study treatment and at the 30 day follow up visit If results are positive the patient is ineligible/must be discontinued from study treatment immediately.

^f^ Follow-up very 12 weeks after start of treatment until objective disease progression as defined by RECIST 1.1, up to 72 weeks, then every 24 weeks relative to date of enrolment. Any other sites at which new disease is suspected should also be appropriately imaged. If an unscheduled assessment was performed and the patient has not progressed, every attempt should be made to perform the subsequent assessments at their scheduled visits.

^g^ All ongoing adverse events/serious adverse events (AEs/SAEs) and any new AEs/SAEs identified during the 30 calendar days follow up period after last dose of study medication must be followed to resolution.

^h^ Sufficient study treatment should be dispensed for at least each treatment period plus overage.

^i^ All anti-cancer treatments (including, but not limited to, chemotherapy and targeted agents), and the investigators opinion of response to them plus the date of progression, post discontinuation of study treatment need to be recorded.

^j^ Only patients on treatment post progression are required to undergo this procedure.

^K^ Patients on treatment post progression are only required to undergo these procedures.

| Table 3 Study Schedule –Follow up Post Discontinuation of Study Treatment | | |
| --- | --- | --- |
| Visit Number | **Off treatment follow up**  **Study treatment discontinued due to reasons other than disease progression**  **Visits every 12 weeks Follow up for 1st progression Tumour assessment visits every 12**  weeks or 24 weeksa | **Time to second progression (PFS2) and Survival for:**  • Patients who have discontinued study treatment due to disease progression  • Patients who have progressed off treatment  • Patients who were on study treatment post progression and / or after primary (PFS) analysis who subsequently discontinued study treatment  Every 12 weeks post discontinuation of study treatment |
| Visit Window | ±7d | ±7d |
| Blood sample for disease specific marker (CA-125) | X |  |
| Tumour Assessment (CT or MRI according to modified RECIST v1.1) a | X |  |
| Adverse Events | X | X |
| ECOG performance status | X | X |
| Subsequent cancer therapy following discontinuation of study treatment ^b^ | X | X |
| Time to second progression |  | X |
| Survival ^cd^ | X | X |

a RECIST follow-up assessments will be performed every 12 weeks (±1 week), up to 72 weeks, then every 24 weeks (±1 week) relative to date of enrolment. Follow-up assessment will include CT or MRI assessments of abdomen and pelvis for all patients. Follow-up chest CT will be performed (in those patients with thoracic lesions or upper abdomen lymphadenopathy identified at baseline assessment). Any other sites at which new disease is suspected should also be appropriately imaged. Patients must be followed until RECIST disease progression. If an unscheduled assessment was performed and the patient has not progressed, every attempt should be made to perform the subsequent assessments at their scheduled visits. Following disease progression further RECIST assessments will not be performed and assessment of disease will be as per local clinical practice.

b All anti-cancer treatments (including, but not limited to, chemotherapy and targeted agents), and the Investigators opinion of response to them and the date of progression need to be recorded.

c The status of ongoing, withdrawn (from the study) and “lost to follow-up” patients at the time of an overall survival analysis should be obtained by the site personnel by checking the patients notes, hospital records, contacting the patients general practitioner and checking publicly available death registries. In the event that the patient has actively withdrawn consent to the processing of their personal data the vital status of the patient can be obtained by site personnel from publicly available resources where it is possible to do so under applicable local laws.

d In addition to their regular 12 weekly contact, patients will be contacted in the 7 days following a specified date (data cut off date) for each survival analysis.

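### Table 2 footnote k leaves out the concomitant-medication/transfusion row (at odds with Section 7.7) and the pregnancy-test row, so neither scheduled check is required for patients kept on olaparib after progression

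*Protocol*

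**What the plan says.** Section 3.9 lists progression as a reason to stop olaparib, but exempts the patient where, in the investigator's "opinion the patient is benefiting from the treatment and does not meet any other discontinuation criteria". Section 7.2 says the same. Footnote a to Table 2 therefore defines the visit schedule for patients "if not progressed and still on treatment, or on study treatment post progression": every 4 weeks up to week 120, then every 12 weeks.

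Footnote k then limits the content of those visits: "Patients on treatment post progression are only required to undergo these procedures". The marker appears on six rows: haematology/chemistry ("Haematology / clinical chemistry^d,k"), CA-125, adverse events ("Adverse Events ^g,k"), olaparib dispensing and return, second progression, and survival. The row "Concomitant medications including blood transfusions" has no marker at all. The pregnancy row reads "Pregnancy test ^e", so it carries e but not k.

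Section 7.7 requires every concomitant medication to be recorded, lowers the olaparib dose while a strong or moderate CYP3A inhibitor is taken, and bars other anti-cancer therapy during study treatment. Footnote e and Section 5.2.5.1 call for pregnancy tests during study treatment at the Table 2 time points and at the 30-day follow-up. Section 6.6.1 requires olaparib to stop at once if a patient becomes pregnant, and Appendix C rates the foetal risk as medium/high.

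**The concern.** Some assessments can sensibly end at progression because they describe the disease. Others are needed for as long as the drug is taken. Footnote k drops two of the second kind while keeping dispensing.

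The medication review is how a site learns at a visit that a patient has started a CYP3A inhibitor (which calls for a lower olaparib dose), has started a prohibited anti-cancer therapy, or has been transfused. Other anti-cancer therapy is most likely to be considered after progression. Transfusion dependence is part of the definition of prolonged haematological toxicity in Section 6.8.1.3, which leads to the bone marrow work-up. Footnote k keeps the blood counts but not the transfusion record needed to interpret them.

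The scheduled pregnancy test is how a pregnancy is found early enough for the stop rule in Section 6.6.1 to help. Section 7.7 also warns that hormonal contraceptives may work less well with olaparib, although Appendix C requires a male condom in addition.

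What is at stake is safety monitoring and the completeness of exposure data in patients treated beyond progression. The PFS analysis is not touched.

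**Working it through.** The protocol gives no figure to reproduce on this point. The check is a reading of the Table 2 markers against the footnotes and the body text, followed by a visit count.

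**1. What footnote k means.** Footnote j, directly above it, says that only patients treated after progression need the procedure it marks. Footnote k places the word differently and says that these patients need only the procedures it marks. So k restricts the schedule; it does not merely label rows that apply to this group.

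**2. Rows with an X in the column for Visit 7 onwards.**

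| Row | Carries k? | Relates to |
| --- | --- | --- |
| Haematology/chemistry | yes | drug exposure |
| CA-125 | yes | disease |
| Adverse events | yes | drug exposure |
| Olaparib dispensed/returned | yes | drug exposure |
| Second progression | yes | outcome |
| Survival | yes | outcome |
| ECOG | no | disease |
| Tumour assessment | no | disease |
| Pregnancy test | no | drug exposure |
| Concomitant medications/transfusions | no | drug exposure |

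Ten rows, six with k, and 10 − 6 = 4 without. The tumour-assessment omission is intended, since Table 3 footnote a says: "Following disease progression further RECIST assessments will not be performed". ECOG can be defended as a disease measure. That leaves two of the four that concern taking olaparib.

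**3. Is the medication row a likely slip?** Three rows have an X in all eight columns of Table 2: haematology/chemistry, adverse events and concomitant medications. The first two carry k and the third does not. No reason is given.

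**4. Table 2 against the body text.**

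- *Concomitant medications.* The duties in Section 7.7 apply while olaparib is taken, with no end at progression. Table 2 with k says the scheduled review is not required. The two are inconsistent.
- *Pregnancy test.* Footnote e and Section 5.2.5.1 intend testing during study treatment but take their time points from Table 2. Once k removes the row, neither text restores the on-treatment tests. This is a gap that fits poorly with Section 6.6.1 and Appendix C, not a formal contradiction. Section 7.7 has no pregnancy-test rule.

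**5. Size per patient.** The duration of olaparib after progression is not in the protocol. Assume 12 to 48 weeks and use the visit intervals in footnote a:

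- wholly before week 120: 12/4 = 3 to 48/4 = 12 visits;
- wholly after week 120: 12/12 = 1 to 48/12 = 4 visits.

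That is the number of medication/transfusion reviews not required per patient, and the number of pregnancy tests not required for a woman of childbearing potential. These counts describe the schedule, not harm.

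**6. Which range applies now.** Planned last enrolment was Q4 2018. Week 120 is 120 × 7 = 840 days later, so on the planned timetable every patient passes it by Q2 2021. Version 4.0 is dated 30 January 2023. If enrolment kept to plan, only the range of 1 to 4 remains for a future amendment; actual enrolment dates are not in the document.

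**The case against.** The strongest reply is that footnote k trims a visit list and does not waive duties stated elsewhere. Section 7.7 still requires concomitant medications to be recorded, and its closing part on other concomitant treatment covers other necessary medication and unplanned procedures. Section 6.8.2.3 still requires dose reductions and interruptions to be entered with reasons. Adverse events, haematology and dispensing all keep k, and Appendix A gives anaemia needing transfusion as an example of an important medical event, so many transfusions would surface anyway. All of this stands, and it makes the loss partial. It does not resolve the inconsistency: the schedule is what prompts the question at a visit, and it tells the site the review is not required.

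On pregnancy, footnote e and Section 5.2.5.1 defer to Table 2, so there is no strict contradiction. The 30-day test and the contraception rules in Section 3.8.2 and Appendix C remain. Given the postmenopausal definitions in Section 3.1 and the usual surgery for this disease, few patients are likely to be of childbearing potential. This also stands and limits the size of the gap. But because the testing text defers to Table 2, no other text fills the gap during treatment.

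It can also be said that k follows no clear logic, so inferring a slip from two rows out of three is weak. CA-125 carries k although Section 5.2.1.3 leaves it to the investigator after progression, and ECOG lacks k although Table 3 asks for it after progression once treatment has stopped. The inference is indeed only suggestive. Equally, a deliberate minimum safety set would hardly mandate a discretionary tumour marker while leaving out the medication review.

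**Conclusion.** The point holds. Read as written, Table 2 does not require the scheduled concomitant-medication/transfusion review or the scheduled pregnancy test at olaparib visits after progression. The first omission is inconsistent with Section 7.7; the second leaves a gap for a drug rated medium/high foetal risk.

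The effect is modest. The number of patients affected cannot be derived from the protocol and is probably small, smaller still for pregnancy testing. The per-patient counts rest wholly on the assumed 12 to 48 weeks of treatment, and the lower range of 1 to 4 is the one likely to matter at the date of version 4.0. Recording duties, adverse-event reporting, haematology and contraception rules continue. Neither the PFS estimate nor its precision changes.

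**What to change.** Add marker k to two rows of Table 2: the concomitant-medication/transfusion row, and the pregnancy-test row for women of childbearing potential.

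As a separate editorial alignment, put an X for the pregnancy test in the 30-day follow-up column, where footnote e and Section 5.2.5.1 already require it but the table shows none.

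The cost is two footnote markers and one table entry. The visits already take place, with bloods, adverse-event review and dispensing, so the added burden is a few eCRF entries and, for women of childbearing potential, a urine or blood test.

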### Second progression (PFS2)

Patients should be assessed every 12 weeks for a second progression (using the patient’s status at first progression as the reference for assessment of second progression). A patient’s progression status is defined according to local standard clinical practice and may involve any of; objective radiological, CA-125, clinical progression or death. The date of PFS2 assessment and investigator opinion of progression status (progressed or non-progressed) at each assessment will be recorded in the eCRF.

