### Patient management post primary analysis

The data cut off for the statistical analysis for the primary objective in the patients enrolled will be at 60% maturity for PFS analysis.

Patients on olaparib at the time of the data cut-off will continue to receive olaparib until they meet any discontinuation criteria as per Section 3.9.

Patients on study treatment will be followed for core safety assessments and disease progression. These patients should be followed according to Table 2 and 3.

All patients (patients still on olaparib and patients withdrawn from olaparib) will be followed for survival and disease progression.

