### Tumour Evaluation

RECIST 1.1 criteria will be used to assess patient response to treatment by determining progression free survival (PFS) times according to the RECIST 1.1 guideline (Eisenhauer et al 2009).

The methods of assessment of tumour burden used at baseline CT or MRI scans of neck, chest, abdomen and pelvis must be used at each subsequent follow-up assessment. Any other areas of disease involvement should be additionally imaged based on the signs and symptoms of individual patients.

Following the baseline assessment, efficacy for all patients will be assessed by objective tumour assessments every 12 weeks after enrolment, up to 72 weeks, then every 24 weeks until objective disease progression as defined by RECIST 1.1. Any other sites at which new disease is suspected should also be appropriately imaged.

If a patient discontinues treatment (and/or receives a subsequent cancer therapy) prior to progression then the patient should still continue to be followed until objective disease progression as defined by RECIST 1.1.

Categorisation of objective tumour response assessment will be based on the RECIST 1.1 criteria of response: CR (complete response), PR (partial response), SD (stable disease) and PD (progression of disease). Target lesion (TL) progression will be calculated in comparison to when the tumour burden was at a minimum (i.e. smallest sum of diameters previously recorded on study). In the absence of progression, tumour response (CR, PR, SD) will be calculated in comparison to the baseline tumour measurements obtained before starting treatment.

For patients with non-measurable disease only at baseline, categorisation of objective tumour response assessment will be based on the RECIST 1.1 criteria of response: CR (complete response), PD (progression of disease) and Non CR/Non PD.

If the Investigator is in doubt as to whether progression has occurred, particularly with response to NTL (non-target lesion) or the appearance of a new lesion, it is advisable to continue treatment until the next scheduled assessment or sooner if clinically indicated and reassess the patient’s status. If repeat scans confirm progression, then the date of the initial scan should be declared as the date of progression.

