### Analysis of the primary variable (s)

PFS will be analysed when approximately 132 progression events have occurred in the study (60% maturity). This analysis will address the primary objective of the trial. The updated results will also be provided at the final analysis.

A Kaplan-Meier (KM) plot of PFS will be presented. Summaries of the number and percentage of patients experiencing a PFS event, and the type of event (progression or death) will be provided along with median PFS and 95% confidence interval.

The analysis on PFS will be based on RECIST 1.1 criteria assessed by investigators, and using all scans regardless of whether they were scheduled or not. The estimated PFS rates at 6 months, 12 months and 24 months will be summarised (using the KM curve) for all patients.

The number of patients prematurely censored will be summarised together with baseline prognostic factors of the prematurely censored patients. A patient is defined as prematurely censored if they had not progressed and the latest scan prior to the date of cut off (DCO) was more than one scheduled tumour assessment interval (+ 2 weeks) prior to the DCO date.

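### Table 3 gives conflicting schedules, one with scans and one without, to patients who stop olaparib unprogressed after the primary PFS analysis

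*Protocol*

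**What the plan says.** Table 3 (section 4.1) sets follow-up after olaparib stops, in two columns.

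- Column 1 covers "Study treatment discontinued due to reasons other than disease progression". It follows patients for first progression, with tumour assessments every 12 or 24 weeks and CA-125. It carries no limit tied to any analysis.
- Column 2 is for PFS2 and survival. Its tumour assessment and CA-125 cells are blank. It records adverse events, ECOG status, subsequent therapy, time to second progression and survival. Its third bullet admits "Patients who were on study treatment post progression and / or after primary (PFS) analysis who subsequently discontinued study treatment".

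The other relevant statements are these.

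- Table 3 footnote a requires RECIST follow-up until progression. Section 5.1.1 requires evaluation until radiological progression whether or not treatment is discontinued.
- Section 5.1.2, on a patient who stops before progression: "then the patient should still continue to be followed until objective disease progression as defined by RECIST 1.1".
- Section 4.4.4, on the period after the primary cut-off: "All patients (patients still on olaparib and patients withdrawn from olaparib) will be followed for survival and disease progression".
- Section 5.2.1.3 continues CA-125 until RECIST progression.
- Section 3.9.1: "Any patient who has not yet shown disease progression at withdrawal from IP should continue to be followed as detailed in Table 2".
- Section 4.4.3 assesses PFS2 with the patient's "status at first progression as the reference for assessment of second progression".
- Section 8.4.2 counts progression for PFS even after the patient has withdrawn from therapy. Section 8.5.1 says of PFS: "The updated results will also be provided at the final analysis".

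**The concern.** A patient still on olaparib and progression-free at the primary cut-off, who later stops for toxicity or by choice, meets the headings of both Table 3 columns. One schedule scans her until first progression. The other does not scan her and asks only for a second progression. The section 3.9.1 pointer does not settle the matter, because the tumour assessment row of Table 2 is empty in both the discontinuation and the 30-day follow-up columns.

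At stake are the updated PFS at the final analysis, overall and in BRCAm patients, and PFS2. If scanning stops when olaparib stops, the patient is censored near treatment stop. That censoring is informative if patients who stop tend to progress sooner than those who continue. Her first progression may also go unrecorded, or be entered as a second one.

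**Working it through.** **The plan's own figures.** Section 8.2 gives 220 patients and a primary analysis at 60% maturity: 0.60 × 220 = 132 events. For an exponential median, 95% CI = median × exp(±1.96/√events).

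- All patients: 8.4 × exp(±1.96/√132) = 7.08 to 9.96 months (stated 7.1 to 10.0).
- BRCAm: 19.1 × exp(±1.96/√27) = 13.10 to 27.85 months (stated 13.1 to 27.9).

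Both reproduce. Nothing in this point changes them.

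**What the disputed words add.** The third bullet has two limbs: on treatment after progression, and on treatment after the primary analysis. Anyone treated beyond progression who then stops is caught by the first limb, whatever the date. Anyone who stops because of progression is already in the column's first bullet. What the second limb adds is the patient who stops after the primary analysis without having progressed.

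**That patient under each instruction.**

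| Instruction | Scans to first progression? |
| --- | --- |
| Table 3, column 1 | Yes |
| Table 3, column 2, third bullet | No |
| Table 3, footnote a | Yes |
| Sections 5.1.1 and 5.1.2 | Yes |
| Section 4.4.4 | Followed for progression, but refers to Tables 2 and 3 for the schedule |
| Section 3.9.1 | Refers to Table 2, whose discontinuation columns show none |

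**PFS2.** Sections 4.4.3 and 8.4.3 define second progression relative to the progression used for PFS. Column 2 has no assessment that would establish a first progression in this patient.

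**How many.** Patients without a PFS event at the primary cut-off: 220 − 132 = 88 (40%). This is an upper bound. It includes patients already off olaparib (column 1), patients who will progress on olaparib (scanned under Table 2), and patients withdrawn or lost. The protocol gives no rate of stopping without progression, so a range is assumed: 50% to 90% of the 88 still on olaparib, of whom 5% to 30% later stop unprogressed.

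- Low: 88 × 0.50 × 0.05 = 2.2 patients (1% of 220).
- High: 88 × 0.90 × 0.30 = 23.8 patients (11% of 220).

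**How much bias.** A simulation of 400 trials per scenario used the protocol's medians (19.1 months in 21% of patients, 8.4 months in the rest). It assumed uniform accrual over 9 months, a final cut near month 51, and every affected patient handled under column 2. The accrual pattern, final cut, stopping rates and hazard ratios are assumptions.

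| Stopping unprogressed | Patients losing scans | Progressions unrecorded |
| --- | --- | --- |
| 10% per year | about 9 | about 6 to 8 |
| 20% per year | about 15 to 17 | about 10 to 15 |

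The 24-month PFS rate with full versus truncated follow-up, by hazard after stopping relative to on treatment:

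- ratio 1, 10% per year: 0.197 vs 0.197, difference 0
- ratio 2, 20% per year: 0.163 vs 0.171, difference 0.8 points
- ratio 3, 20% per year: 0.147 vs 0.162, difference 1.5 points

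**Why the 24-month rate is the exposed summary.** In the simulation the 132nd event falls at about month 16 to 18, when no patient has 24 months of follow-up. On the protocol's planned dates (first patient Q2 2018, PFS analysis Q2 2020) the longest possible follow-up is about 27 months. The 24-month rate in section 8.5.1 therefore rests largely or wholly on data collected after the primary analysis.

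**The case against.** The strongest reply is that the intention is plain. Column 1 fits this patient exactly. Column 2's title presupposes a first progression, and its second bullet implies the sequence of column 1 until progression and column 2 afterwards. Footnote a and sections 4.4.4, 5.1.1 and 5.1.2 all point to scanning, against one limb of one bullet. Footnote f of Table 2 also asks for scans until progression, so the section 3.9.1 pointer looks like a cross-reference slip. The consequence is limited to a descriptive update in a single-arm study without a hypothesis test.

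Most of this stands. A reader might infer that Table 3 removes these patients from scanning, so that updated PFS and PFS2 cannot be measured. The documents do not support that. The patients fit both columns, those still on olaparib keep their Table 2 scans, those who stopped before the cut-off remain in column 1, and Table 3 footnote b still collects a progression date alongside subsequent therapy. Nor is 88 of 220 the number affected; it is only a ceiling.

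The reply does not remove the contradiction. The bullet names the post-primary period explicitly, so a site could reasonably treat it as the specific rule, and section 4.4.4 sends the reader back to the tables. The fallbacks are also partial. A progression date noted with later therapy is not a scheduled RECIST assessment. A death counts as a PFS event only within the missed-visit limit of section 8.4.2; beyond 26 weeks from the last RECIST assessment it is censored.

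**Conclusion.** The point holds as an internal contradiction: for patients who stop olaparib unprogressed after the primary analysis, Table 3 conflicts with itself and with the body text. If sites follow the column 2 bullet, updated PFS (overall, BRCAm and the 24-month rate) is incompletely measured for this subset, and their PFS2 is ill-defined. The primary 132-event analysis and its planned precision are untouched.

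The likely effect is modest. The counts rest on stopping rates the protocol does not give. The bias is zero if progression is no faster after stopping, and reaches 1.5 points only with an assumed threefold hazard, 20% per year stopping, and every site following the bullet. It should be corrected because the wording is wrong as it stands and correction is cheap.

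**What to change.** Reconcile the passages in one amendment.

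1. In the third bullet of Table 3 column 2, delete the alternative that refers to the primary PFS analysis, so that the column is limited to patients with RECIST 1.1 progression.
2. State in column 1 that it applies to every patient who stops olaparib without RECIST progression, before or after the primary analysis, until progression.
3. In section 3.9.1, change the pointer for unprogressed patients from Table 2 to Table 3.

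The cost is amendment wording and notice to sites. The practical burden is 12- or 24-weekly imaging for a small number of off-treatment patients, which sections 4.4.4, 5.1.1 and 5.1.2 already call for. No sample-size or analysis figure changes.
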